### Data analysis

A score will be generated from each tool at each age of assessment. For example, a motor optimality score will be generated for each child using their GMA assessment data at 3 months, which will be analysed for predictive ability of the primary outcome at 24 months. A similar approach will be adopted with the other tools assessed at different ages. Assuming the composite primary outcome is the gold standard to measure NDI, sensitivity and specificity will be computed for each score at each age using different cut-offs. The age-specific approach will inform if any age(s) are better suited for administration of that tool to predict NDI at 24 months. Sensitivity versus 1-specificity will be plotted to generate ROC curves. To identify optimum threshold values for defining positive cases, various cut-offs of age-specific scores will be used to generate age-specific ROC curves and estimate the corresponding AUROCs which will be further explored to maximise statistical efficiency with clinical advantage.

Stata’s ROCREG procedure will be used, which allows for clustering of repeated measurements within participant and accounts for the influence of covariates. HINE and GSED’s performance will be assessed using the Stata ROCCOMP procedure, which specifically allows direct comparison of AUROCs in dependent samples at two different ages. Finally, we will compute AUROC for each instrument-age combination using the Stata ROCTAB procedure that computes sensitivity, specificity and percentage of cases correctly classified for each score on the predictive instrument.

Analysis to examine GSED’s predictive validity for NDI at 24 months will follow the same procedures as described earlier. Additionally, GSED construct validity at each age will be assessed by comparing it to the MSEL using Pearson correlation coefficient and mixed effects linear regression models. Covariates to be included in the adjusted models are prespecified in the study protocol and include maternal education, caregiver mental health (measured by the SSQ), birth weight, HIV exposure status, postnatal onset of serious health conditions and child home environment (measured by the FCI). These models will also allow exploration of potential interactions between GSED scores and the prespecified covariates.

To check consistency between dual scored items/scores, we will estimate various reliability measures. For continuous total or domain scores (eg, HINE, MSEL), intraclass correlation coefficients will be estimated. For categorical outcomes, Cohen’s kappa (or weighted kappa for ordinal categories) and percentage agreement will be quantified.

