### Study participants

A target sample of 696 infants will be recruited, with a final study sample size goal of n=600 completing study visits at 24 months of age. Inclusion and exclusion criteria by risk stratum are in table 1.

**Table 1 T1:** Participant inclusion and exclusion criteria

Risk stratum	Target sample	Recruitment location	Description	Exclusion criteria
Low	250	Local clinics	No concern for perinatal asphyxia	Preterm birth (<37 completed weeks’ gestation) Low birth weight (<2500 grams) Confirmed sepsis, meningitis, severe jaundice (ie, infants with bilirubin level exceeding 425 IU (25 mg%) or symptoms of acute bilirubin encephalopathy) Significant congenital malformation, genetic syndrome Congenital infection by serology, culture or consistent clinical findings Residence outside urban/peri-urban Harare Primary caregiver <18 years
Moderate	223	Local clinics Sally Mugabe Central Hospital postnatal ward NNU Prior study cohort*	Did not cry at birth Required resuscitation Thompson score remained <6^37 38^	
High	223	NNU Prior study cohort*	Experienced perinatal asphyxia Admitted to the NNU with neonatal encephalopathy (ie, Thompson score 6 or more at any point after birth) Survived to hospital discharge without a potentially confounding illness	

* A parallel study focused on the Helping Babies Breathe/Essential Newborn Care intervention followed a cohort of high-risk infants until 6 months of age. A subset of these infants was approached for participation in the ChiDO study.

NNU, neonatal unit.

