### Sample size estimates

Each tool’s ability to predict NDI (aims 1 and 2) will be assessed using sensitivity, specificity and area under the receiver operating characteristic (AUROC) curve. Based on Ugandan data,^30^ 1.3% of low-risk and 29% of high-risk infants are expected to have NDI—approximately three and 59 children, respectively. For medium-risk infants, local unpublished data suggest a 5% NDI rate, or about 10 children, constituting an overall incidence of 12%. Assuming about 15% loss to follow-up, the two-sided 95% CIs for 0.85 sensitivity, specificity and AUROC estimable from this study will be 0.75 to 0.92, 0.82 to 0.88 and 0.79 to 0.91, respectively (table 2). Keeping other parameters unchanged, if higher loss to follow-up leads to a smaller analytic sample, the 95% CIs estimable from this study will be wider.

**Table 2 T2:** Precision of point estimates for sensitivity, specificity and area under the ROC curve for n=600 (95% CIs)

Statistic	Estimate	CI	Estimate	CI	Estimate	CI
Sensitivity	0.75	0.64 to 0.86	0.85	0.76 to 0.93	0.95	0.87 to 0.99
Specificity	0.75	0.71 to 0.79	0.85	0.82 to 0.88	0.95	0.93 to 0.97
AUROC	0.75	0.68 to 0.82	0.85	0.79 to 0.91	0.95	0.92 to 0.99

AUROC, area under the receiver operating characteristic; CI, confidence interval.

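### On the plan's own rates, enrolment stratum alone has an AUROC of about 0.80, so a pooled AUROC up to about 0.85 does not separate a tool from the recorded risk group, and no stated analysis tests the gain.

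*Protocol article*

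**What the plan says.** Table 1 (Study participants) sets recruitment targets of 250 low-risk, 223 moderate-risk and 223 high-risk infants. In all, 696 are to be enrolled so that 600 complete the 24-month visit.

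Sample size estimates gives the expected outcome rates: "1.3% of low-risk and 29% of high-risk infants are expected to have NDI", that is "approximately three and 59 children, respectively". For the middle stratum, "local unpublished data suggest a 5% NDI rate, or about 10 children, constituting an overall incidence of 12" per cent. The precision statement is for a single sample: "Assuming about 15% loss to follow-up", the 95% intervals at 0.85 for sensitivity, specificity and AUROC "will be 0.75 to 0.92, 0.82 to 0.88 and 0.79 to 0.91, respectively". Table 2 gives the same kind of figures for n=600, again without a split by stratum.

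Under Data analysis, "sensitivity and specificity will be computed for each score at each age using different cut-offs", and AUROCs follow by tool and age. Under Missing data, every ROC analysis takes all participants with the 24-month diagnostic examination. The ROCREG sentence says covariates are accounted for but names none. The only covariate list comes in the next paragraph, after the GSED–MSEL construct-validity models. It contains maternal education, caregiver mental health, "birth weight, HIV exposure status, postnatal onset of serious health conditions and child home environment". Risk stratum is not on it, but the list is worded as open and points to the full study protocol.

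The article states no within-stratum AUROC, no stratum-adjusted AUROC and no comparison of a tool with stratum as a predictor.

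**The concern.** By design, most expected cases sit in one stratum and most non-cases in the other two. A score that only reflects whether a child had neonatal encephalopathy will rank cases above non-cases in the pooled sample, even if it says nothing about which encephalopathic infants go on to NDI. The pooled AUROC therefore mixes two things: the difference between strata, already recorded at enrolment, and the tool's discrimination among children of similar recorded risk.

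The second matters for how the results will be used. Significance and relevance looks ahead to earlier detection, clinical use and extension to other at-risk groups, where the practical question is which at-risk infants will have NDI. Cut-offs chosen on the pooled curve, including the preliminary GSED thresholds in the second aim, also carry a specificity that depends on the recruitment proportions.

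**Working it through.** **Inputs.** Targets 250/223/223, total 696 (Table 1). Rates 1.3%, 5%, 29%; counts 3, 10, 59; overall incidence 12%; n=600 (Sample size estimates, Table 2).

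**1. Reproduce the plan's own figure.** Cases: 3 + 10 + 59 = 72, and 72/600 = 12.0%, leaving 528 non-cases. Hanley–McNeil standard error for AUROC A with m cases and n non-cases:

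SE² = [A(1−A) + (m−1)(Q₁−A²) + (n−1)(Q₂−A²)]/(mn), where Q₁ = A/(2−A) and Q₂ = 2A²/(1+A) are the method's two terms.

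For A = 0.85, m = 72, n = 528: Q₁ = 0.7391, Q₂ = 0.7811, SE = 0.0291. Half-width 1.96 × 0.0291 = 0.057; interval 0.793 to 0.907, matching the stated 0.79 to 0.91. The 0.75 and 0.95 columns of Table 2 also reproduce, to within 0.01.

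**2. AUROC of stratum alone.** Scale the targets to 600: 215.5, 192.2, 192.2.

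| | Low | Moderate | High |
|---|---|---|---|
| Expected cases | 2.8 | 9.6 | 55.7 |
| Share of cases | 0.041 | 0.141 | 0.818 |
| Expected non-cases | 212.7 | 182.6 | 136.5 |
| Share of non-cases | 0.400 | 0.343 | 0.257 |

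AUROC = Σ (share of cases in stratum) × (share of non-cases in lower strata + ½ share in the same stratum)

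= 0.041 × 0.200 + 0.141 × (0.400 + 0.172) + 0.818 × (0.743 + 0.128)

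= 0.008 + 0.081 + 0.713 = 0.802.

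With the stated counts 3/10/59 in the same stratum sizes it is 0.804. With 200 per stratum it is 0.796 using the rates and 0.795 using the counts. The range is 0.79 to 0.80. Equal loss across strata does not change it.

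**3. High-risk stratum as a positive test.** Sensitivity 59/72 = 0.82. Specificity is 1 − 0.257 = 0.74; across the same readings it runs from 0.73 to 0.75.

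**4. Where the pooled interval clears the benchmark.** With 72 and 528, the lower 95% limit is 0.793 at an estimate of 0.85, 0.799 at 0.855 and 0.801 at 0.857. So about 0.857 is needed. Of Table 2's three AUROC columns, 0.75 (0.68 to 0.82) and 0.85 (0.79 to 0.91) have intervals that contain 0.80; 0.95 (0.92 to 0.99) lies clearly above it.

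**5. Sensitivity to the expected rates (assumed variations).** Stratum-only AUROC is 0.77 if the high-risk rate is 20%, 0.82 if it is 35%, and 0.77 if the moderate rate is 10%.

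**6. Illustration of the mixing (assumed, not in the documents).** Take normal scores with equal variance and equally spaced stratum means, and a within-stratum AUROC of 0.70. If the mean moves 0.75 to 1.5 SD from low to high stratum, the pooled AUROC is 0.77 to 0.82.

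**7. Precision within strata.** High-risk, about 56 cases and 137 non-cases: half-width 0.067 at AUROC 0.85 and 0.081 at 0.75, against 0.057 and 0.068 pooled. In the other strata, exact 95% intervals for sensitivity would be 0.29 to 1.00 for 3 of 3 low-risk cases and 0.44 to 0.97 for 8 of 10 moderate-risk cases.

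**The case against.** Four points count on the other side, and each limits what can be said.

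- **The pooled result can still be informative.** A reader might infer that it can never show that a tool adds anything. That is too strong. On the planned rates NDI risk rises from stratum to stratum, so a score with no information beyond stratum cannot exceed about 0.80 in expectation. A pooled estimate with a lower limit above that would be evidence of more.
- **Adjustment is not ruled out.** A reader might also infer from the covariate list that stratum is left out of ROCREG. The list follows the GSED–MSEL models, is open, and refers to a full protocol that is not shown. Nor does the 0.80 arise from a missing covariate; it follows from the recruitment mix and the expected rates.
- **The stated aim is prediction across the risk spectrum.** Gain over risk group is not claimed, and separating known risk groups is itself a GSED hypothesis, with its own generalised estimating equations analysis in the abstract. Pooled accuracy answers the stated aim. Replacing it as primary would change the estimand and the precision basis, which the documents do not call for.
- **Stratum is not free information.** Table 1 separates moderate from high risk by the Thompson score at any point after birth, plus neonatal unit admission, and the introduction reports missed early detection despite a referral system. Stratum is better described as recorded at enrolment than as known at birth without any tool.

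All four stand. They leave untouched the 0.80 benchmark, its place inside the interval at the plan's own example value, and the absence of any stated comparison with it.

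**Conclusion.** The point holds as an improvement to analysis and reporting; it does not invalidate the planned analysis. On the plan's own rates and allocation, stratum alone reaches an AUROC of 0.79 to 0.80. A pooled AUROC up to about 0.85 would therefore not, on its own interval, distinguish a tool from the risk group on the enrolment form.

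This rests on the expected rates being roughly right (0.77 to 0.82 under the variations shown) and on treating the benchmark as a fixed number. In the data it would be estimated from the same children, so a paired comparison is the proper test, and the 0.857 threshold is only a guide. The illustrated inflation depends on an assumed stratum shift and should not be read as a documented size.

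**What to change.** Keep the pooled AUROC for the stated aim, and label it, and any cut-off derived from it, as specific to this enriched mix. Prespecify alongside it, before outcome data are analysed:

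1. the AUROC within the high-risk stratum and/or a stratum-adjusted AUROC, with risk stratum as a covariate in ROCREG;
2. the stratum-only AUROC as benchmark, with each tool's gain over it and a confidence interval.

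State that accuracy within the low-risk stratum (about 3 cases) and the moderate-risk stratum (about 10 cases) cannot be estimated with useful precision. If the full protocol already adjusts for stratum, say so in the article's analysis section.

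Stratum is already recorded at enrolment (Table 3), so no new data are needed. The cost is a little more analysis and wider high-risk intervals: half-width about 0.07 at AUROC 0.85 and 0.08 at 0.75, against 0.057 and 0.068 pooled.

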The objective of this study is to validate three neurodevelopmental assessment tools—the GMA, HINE and GSED—among a longitudinal cohort of children across the NDI risk spectrum related to perinatal asphyxia and neonatal encephalopathy in Harare, Zimbabwe. The study setting includes the Children’s Rehabilitation Unit (CRU), which opened in 1986 and provides children with developmental risks, delays or disorders and their families with free diagnostic and therapeutic services. Local data from the CRU Developmental Disability and Cerebral Palsy registers identify perinatal asphyxia as the most common attributed aetiology, leading to 33% of disability and 48% of CP.^22
23^ In the 10 years between 2006 and 2015, incidence by birth year (birth prevalence) of CP associated with perinatal asphyxia alone ranged from 1.0 to 2.3 per 1000 live births. However, despite a national at-risk referral system designed to identify infants at risk of NDI, CRU data between 2006 and 2015 also indicate a significant portion of children missed opportunities for early detection and intervention.^22
23^

Our specific aims are to:

Assess the ability of the GMA at 3 months and HINE at 3 months, 6 months, 12 months and 18 months to predict NDI at 24 months of age.Assess the validity of the GSED and establish preliminary GSED threshold scores for predicting NDI at 24 months of age.

We hypothesise that both the GMA and HINE will be feasible to administer and show strong predictive ability for NDI at 24 months of age and that the GSED will show construct validity, discriminate between known risk groups and have predictive ability over multiple ages from 3–18 months for children with and without NDI at 24 months of age.

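### Cut-offs and preferred ages are chosen and evaluated on the same children (about 72 cases) with no explicit rule or internal validation described, so the sensitivity singled out will be optimistic by an amount that depends on the rule

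*Protocol article*

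**What the plan says.** The Data analysis section computes sensitivity and specificity for every tool at every age over a range of cut-offs. It then says: "To identify optimum threshold values for defining positive cases, various cut-offs of age-specific scores will be used to generate age-specific ROC curves". The only guide to what counts as optimum is that the analysts will "estimate the corresponding AUROCs which will be further explored to maximise statistical efficiency with clinical advantage". On timing it says: "The age-specific approach will inform if any age(s) are better suited for administration of that tool".

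The Missing data section puts the children who complete the 24-month diagnostic examination into all ROC analyses. No hold-out sample is described.

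Thresholds are a stated product for one tool: aim 2 is to "establish preliminary GSED threshold scores for predicting NDI at 24 months of age". The word preliminary is attached to GSED only, whereas the search for optimum thresholds in the Data analysis section covers all the tools.

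On numbers, Sample size estimates expects "1.3% of low-risk and 29% of high-risk infants are expected to have NDI—approximately three and 59 children, respectively", and for the moderate-risk stratum "local unpublished data suggest a 5% NDI rate, or about 10 children, constituting an overall incidence of 12" per cent.

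**The concern.** A cut-off picked because it performs well in a sample partly fits the chance features of that sample. Accuracy computed at that cut-off in the same children is biased upward, and its ordinary confidence interval covers less often than stated. Choosing the age that looks best adds a second layer. The bias falls mainly on sensitivity, because there are far fewer cases than non-cases.

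The scope for selection is real. HINE is given at four ages before 24 months (3, 6, 12 and 18 months), the GSED Short Form at the same four, and the Long Form at three. GMA is given once, so only cut-off selection applies to it.

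What is at stake is the sensitivity that readers attach to a recommended threshold. The Significance section looks ahead to clinical use and to other at-risk groups. If the quoted sensitivity is too high, a programme adopting the threshold will miss more affected children than it expects.

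**Working it through.** **Inputs from the article.** Expected cases: 3 + 10 + 59 = 72. With n = 600 at 24 months, 72/600 = 12%, leaving 600 − 72 = 528 non-cases.

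**Reproducing the stated precision at 0.85.**
- Sensitivity, n = 72: exact limits 0.746 to 0.923, Wilson limits 0.750 to 0.915. The text gives 0.75 to 0.92.
- Specificity, n = 528: 0.85 ± 1.96 × √(0.85 × 0.15/528) = 0.82 to 0.88. This agrees.
- AUROC, Hanley–McNeil standard error 0.0291: 0.85 ± 1.96 × 0.0291 = 0.793 to 0.907. This agrees.

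The stated intervals for sensitivity and specificity are thus ordinary binomial limits, which take the cut-off as given. (Table 2 prints 0.76 to 0.93 for the same sensitivity, which differs slightly from the text; nothing here depends on it.)

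**Simulation of the selection step.** Assumptions, none of them from the article: non-case scores N(0, 1), case scores N(d, 1), with d = √2 × Φ⁻¹(AUROC); 72 cases and 528 non-cases; 3,000 data sets per setting. In each data set the cut-off t is chosen by the rule and apparent sensitivity is read off. The true value is 1 − Φ(t − d), and optimism is apparent minus true. For best of four ages, all four are equally good in truth, with within-child correlation 0.5 or 0.8.

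Mean optimism in sensitivity, in percentage points:

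| Rule | Ages | AUROC 0.75 | AUROC 0.85 | AUROC 0.95 |
|---|---|---|---|---|
| Youden | one | 4.8 | 3.8 | 3.1 |
| Youden, score in 0.25 SD steps | one | 3.0 | 2.3 | 1.8 |
| Closest to corner | one | 3.2 | 3.0 | 2.5 |
| Fixed specificity 0.85 | one | about 0.2 | about 0.2 | about 0.2 |
| Youden | best of four | 6.5 to 8.2 | 5.8 to 7.4 | 4.6 to 5.9 |
| Fixed specificity 0.85 (correlation 0.5) | best of four | 3.1 | 3.6 | 2.3 |

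A fixed-sensitivity rule at one age gives about 1 point at AUROC 0.85.

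**Other measures.** Specificity optimism is at most about 1 point. AUROC optimism is essentially 0 at one age. For the best of four ages it is about 0.5 to 2 points with equal score variances, and up to about 3 with unequal variances.

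**Coverage at AUROC 0.85.** The nominal 95% exact interval for sensitivity at the Youden cut-off covers about 92 to 93% at one age. It covers about 81% with the best of four ages at correlation 0.5.

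**Scale.** The stated sensitivity interval has half-width (0.92 − 0.75)/2 = 0.085. The one-age Youden bias at AUROC 0.85 is 3.8/8.5 = 45% of that.

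**Does the remedy work?** Bootstrap correction was run at AUROC 0.85 with Youden, 100 resamples per data set, repeating the whole selection in each resample:
- One age: apparent 0.795, corrected 0.768, true 0.756. Share removed: (0.795 − 0.768)/(0.795 − 0.756) = 0.027/0.039 = 69%.
- Best of four ages, correlation 0.5: apparent 0.825, corrected 0.779, true 0.758. Share removed: 0.046/0.067 = 69%.

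**The case against.** The best defence is that this is a condensed article. It refers to a fuller study protocol for its covariates, and internal validation may be set out there or in an analysis plan. That stands as far as it goes: a reader must not infer that no validation is planned. But the point also rests on what the article does state. It describes data-driven choice of threshold and age on one set of children, and the criterion it gives does not say what will be maximised.

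It is also fair that values tabulated at every cut-off, and AUROCs reported for every age, carry no selection bias. Only the figures singled out at a chosen threshold or age do. Aim 2 already calls the GSED thresholds preliminary, which moderates the claim for that tool but not for GMA or HINE.

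Three stronger readings are tempting and are not supported:
- **A fixed bias of about 4 points.** That figure needs a Youden rule, a near-continuous score and a single age. The article names no such rule, and the figure leaves out age selection.
- **Table 2 is invalid as a whole.** It is a planning table at hypothetical values. AUROC involves no cut-off and specificity barely moves, so only the sensitivity row is materially affected.
- **Percentage correctly classified will drive the choice.** The article lists it as an output of the Stata ROCTAB procedure, not as a selection criterion.

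**Conclusion.** The point holds in a limited form. Sensitivity singled out at a threshold or age chosen by the described procedure will be optimistic. With about 72 cases the expected size is:
- about 0 to 1 point under a fixed-specificity or fixed-sensitivity rule at one age;
- about 3 to 5 points under Youden at one age with a near-continuous score, or 2 to 3 with a coarse score;
- about 5 to 8 points under Youden with the best of four equally good ages.

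These ranges rest on assumed binormal scores, AUROC 0.75 to 0.95 and within-child correlation 0.5 to 0.8. The four-age figures also assume that the ages are equally good, so that the choice among them is pure chance. The article gives no figure for this bias and its inputs do not fix one. The width of the range is itself the argument for settling the rule before the curves are seen. This is a correctable weakness in reporting and analysis, and it does not threaten the study design.

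**What to change.** 1. Pre-specify one selection criterion for cut-offs, for example the highest specificity subject to a stated minimum sensitivity, and one criterion for preferring an age.
2. Repeat the whole selection, cut-off and age together, inside a bootstrap or cross-validation. Report apparent and optimism-corrected sensitivity and specificity, with confidence intervals from the same procedure.
3. Call the thresholds preliminary for GMA and HINE as well as GSED.
4. Add a note that the sensitivity row of Table 2 is precision at a cut-off fixed beforehand.

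If the full protocol or analysis plan already contains the first two items, a sentence saying so settles them.

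The cost is a little more code, slightly lower reported sensitivity and wider intervals; no new data are needed. The correction is partial (about two thirds of the optimism was removed in the simulation), which is why the preliminary label should stay even after it is applied.
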